## 2. Materials and Methods

### 2.1. Study Design

This project will be a pilot study to determine the viability, sample size, cost, and duration of the study. Additionally, this project has been designed in order to “demonstrate that the planned measurements, the data collection instruments, and the data management system are feasible and effective” [57]. If this study proves to be successful, it will be performed with a larger sample from different work settings.

This study will be observational, analytical, and longitudinal. That is, in this study, different variables of the population under study will be observed and recorded without intervention, and with the aim of establishing causal associations between variables. It is considered longitudinal because the variables will be followed for six months, with continuous recording and monitoring of physical activity and the quality of sleep (wristbands). Variables related to work stress, quality of life, and perception of the quality of sleep and the level of physical activity (specific evaluation tools) will also be specifically measured [57]. This study protocol will follow the SPIRIT 2013 guidelines (See File S1) [58].

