### 2.4. Justification of Sample Size

This pilot study is being suggested in order to determine the feasibility, time, and cost required for a subsequent study, as well as to demonstrate that the selected measurements and instruments are feasible and effective, and to determine, based on the results, the optimal frequency, intensity, and duration of the study.

Likewise, by carrying out this pilot study, we will gain information about the standard deviation and the proportion of participants with the specific characteristics needed for this study, which will allow us to carry out the calculation of the sample size.

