### 2.6. Data Collection and Management

Prior to any other data, socio-demographic features of the participants considered as relevant will be collected using a record sheet of our own elaboration. This questionnaire includes questions regarding age, gender, marital status, residential environment, cohabitation unit, educational level, profession, socio-economic level, working hours, overtime working hours, level of perceived stress, other non-work-related stress factors, actions oriented to stress reduction, and medication intake.

Data will be collected from different sources (Figure 1). For biometrical data, a Xiaomi Mi Band 3 will be worn by all the participants for six months to measure their physical activity (steps), sleep (hours of sleep and sleep stages), and heart rate (bpm). A self-developed data collection system will be installed in one of the computers of the research center, capturing the data from the wristbands via Bluetooth every time they walk nearby and storing it in an Structured Query Language (SQL) database [59]. When the data is analyzed, it will be retrieved by the SQL database in which it was stored. The data will be exported through CSV in a detailed or accumulated way for analysis in any statistical program.

The Research Electronic Data Capture Consortium (REDCap), a safe web application to create and manage online surveys and databases [60], will be used to digitally create the questionnaires and tests explained below, which will be sent to the participants to fill out.

In this study, participants will complete a set of assessment tools and a self-made questionnaire associated with work overload, sleep, and physical activity. These assessment tools will be filled in at the beginning and end of the study, while the self-made questionnaire will be answered throughout the study. This information is shown in Table 1.

The scales to be completed are: (1) the EQ 5D-5L, which evaluates mobility, personal care, daily activities, pain/discomfort, anxiety/depression, and global status at the moment of assessment [61], (2) the PSQI, which analyzes the quantity, quality, duration, latency, and efficiency of sleep [62], (3) the STAI, which evaluates the presence of anxiety [63], and (4) the PSS-10, which measures the degree to which, during the last month, people have felt annoyed or worried or, on the contrary, have felt confident in their ability to control their personal problems [64].

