### 2.7. Data Analysis

The statistical treatment of the data will be performed with the statistical package IBM SPSS Statistic version 22 (IBM, Chicago, IL, USA). The significance level for hypothesis testing is set at 5%. The numerical variables will be expressed as the mean (M) and standard deviation (SD), including range, minimums, and maximums, while the categorical variables will be shown with their absolute frequency and valid percentage. In addition to the simple description of the data and variables studied, inferential analyses will be conducted in order to determine possible significant relationships between the variables of the study, or to allow the contrast of hypotheses. The Kolmogorov–Smirnov test will be applied to check that the variables behave as a normal distribution [65]. If not, non-parametric tests will be used in the subsequent analysis. The association of numerical variables will be analyzed with the Pearson or Spearman’s Rho correlation test, depending on the distribution of the sample. To assess the association of categorical variables, the Chi-square test will be applied, or the likelihood ratio in the case that the frequencies observed are less than 5%. In the case of the association between quantitative and qualitative variables, the comparison of means will be made with Student’s *t*-test and analysis of variance (ANOVA) or Mann–Whitney and Kruskal–Wallis’ U test, as appropriate [66]. Finally, and in order to determine whether there are significant and relevant differences between the results of the evaluations performed (initial, intermediate, and final), the Wilcoxon test will be applied [66]. Data analysis includes the cleaning or pre-processing, description, and processing of the stored data. The final objective of these steps is to obtain information for decision making. During pre-processing, erroneous data are removed or corrected to avoid bias in the results. Subsequently, a descriptive statistical study which summarizes certain relationships and distributions in a simple way will allow us to choose which processing strategy to adopt.

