## Figures and Tables

**Figure 1 ijerph-18-01413-f001:**
[figure not shown]
Registration and capture of biometric data and the assessment process.

**Table 1 ijerph-18-01413-t001:** Measuring assessment tools.

Instrument	Data	Delivery Phase
EuroQol-5D-5L (EQ 5D-5L)	Quality of life	Beginning, follow-up, and completion
Pittsburgh Sleep Quality Index (PSQI)	Sleep habits	Beginning, follow-up, and completion
State-Trait Anxiety Inventory (STAI)	Anxiety	Beginning, follow-up, and completion
Perceived Stress Scale-10 (PSS-10)	Stress	Beginning, follow-up, and completion
Stress Questionnaire	Work stress factors and daily functioning	Daily (3 items) and weekly (4 items)

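### The Wilcoxon test named for change across three assessment rounds compares only two, and the article disagrees with itself on how many rounds there are

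*Protocol article*

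**What the plan says.** The protocol article, section 2.7 (Data Analysis), closes its list of inferential methods with the comparison of assessment rounds: for "differences between the results of the evaluations performed (initial, intermediate, and final), the Wilcoxon test will be applied". No other test is named for that comparison. The same section says "The significance level for hypothesis testing is set at 5"% and names no adjustment for repeated comparisons.

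Table 1 gives the delivery phase of EQ 5D-5L, PSQI, STAI and PSS-10 as "Beginning, follow-up, and completion", which is three rounds. Section 2.6 (Data Collection and Management) says of the same scales: "These assessment tools will be filled in at the beginning and end of the study". That is two rounds.

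Methods for more than two groups do appear in 2.7, but for another purpose: "In the case of the association between quantitative and qualitative variables, the comparison of means will be made with Student’s *t*-test and analysis of variance", with Mann–Whitney and Kruskal–Wallis as the non-parametric counterparts. These treat the groups as independent and do not cover repeated rounds on the same workers.

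**The concern.** The test and the comparison do not match. A Wilcoxon test takes two sets of values. The signed-rank form is the natural reading, because Mann–Whitney is named separately, but the rank-sum form is a two-sample test as well. Neither can answer, in one test, whether a scale changed over three rounds.

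An analyst who follows the sentence has to choose which pairs to test, how many, and how to combine the answers, and the article gives no rule. The result could then depend on a choice made after the data are seen, and a change could be claimed on any one of three nominal 5% tests. This comparison is the one place in 2.7 where change across rounds is tested, in a study described in 2.1 as longitudinal ("It is considered longitudinal because the variables will be followed for six months").

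**Working it through.** **1. Number of rounds.** Section 2.7: three ("initial, intermediate, and final"). Table 1: three. Section 2.6: two. Three is better supported, but the places conflict, and the conflict decides whether the named test fits.

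**2. Number of pairs.** With k = 3 rounds there are k(k − 1)/2 = 3 × 2/2 = 3 pairs per scale. With k = 2 there is one pair, and a paired Wilcoxon test is suitable.

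**3. Inputs.** From the article: significance level 5%, three rounds, Wilcoxon test, no adjustment. Assumed, because the article does not give them: two-sided tests; n = 20, 30, 50 or 100; between-round correlation 0.3, 0.5 or 0.8, either equal for all pairs or decaying with time (AR(1)); normal data without ties; no missing rounds; no true change. On sample size, section 2.4 says only that the pilot will supply information "which will allow us to carry out the calculation of the sample size".

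**4. The stated 5%, for one pair.** Simulation with 40,000 runs per setting gives 4.7–5.1% for initial versus final. A single Wilcoxon test therefore holds its level.

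**5. At least one false positive on one scale.**
- Three pairs, if independent: 1 − (1 − 0.05)³ = 1 − 0.857 = 14.3%. Upper bound: 3 × 0.05 = 15%.
- Three pairs, simulated: 11.7–12.6%. This is below 14.3% because the three differences are linked (any two determine the third).
- Two pairs against the initial round, if independent: 1 − 0.95² = 9.75%. Simulated: 8.4–9.2%.

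**6. The same simulation under alternatives.** The first two rows are the settings with the highest and lowest three-pair error; the third is a middle case.

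| Setting | One pair | Any of 3 pairs | Any of 2 vs initial | Friedman | Pairs only after Friedman | Pairs at 0.05/3 |
|---|---|---|---|---|---|---|
| equal 0.8, n = 20 | 5.0% | 12.6% | 9.2% | 5.4% | 4.5% | 3.9% |
| AR(1) 0.8, n = 20 | 4.9% | 11.7% | 8.4% | 5.6% | 4.5% | 3.6% |
| equal 0.5, n = 50 | 4.9% | 12.3% | 9.1% | 4.8% | 4.1% | 4.2% |

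Over all 24 settings, Friedman gives 4.7–5.6%, pairs tested only after a significant Friedman test 3.9–4.5%, and Bonferroni at 0.05/3 = 0.0167 gives 3.6–4.4%. The simulation error of a 12% figure is √(0.12 × 0.88/40,000) ≈ 0.16 percentage points, so the gap from 5% is not noise.

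**7. Is the gate enough?** With exactly three rounds, once the overall hypothesis of no change is false, at most one of the three pairwise hypotheses can be true. Testing pairs only after an overall rejection therefore needs no further adjustment within a scale.

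**The case against.** The best defence is that the sentence may be harmless. Section 2.6 says the scales are completed at the beginning and end; on that reading there is one pair and the Wilcoxon test is suitable. This stands as a reason to reconcile the places first. It does not clear section 2.7, which itself names three evaluations.

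It can also be said that the article claims only a 5% level per test, that each Wilcoxon test keeps it, and that nothing says all three pairs will be tested. This is right. A reader might infer that the false-positive rate of the plan as written is well above 5%; the text does not support that without the condition that several pairs are tested unadjusted.

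The study is a pilot for feasibility and sample-size inputs. None of the listed objectives is about change between rounds, and the comparison comes last among the inferential tests in 2.7. A reader might take it for the main longitudinal result, but the article does not say so. This limits the weight of the point. It does not remove it, because 2.7 does plan to judge these differences by significance.

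Finally, 2.7 brings in non-parametric tests when normality fails, yet fixes Wilcoxon for the rounds without a parametric alternative. This is at most a small inconsistency: the section does not restrict such tests to that case, and a signed-rank test is valid for normal data.

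**Conclusion.** The mismatch between a two-sample test and a three-round comparison is stated in the text and needs no assumption. It is not a detail left to a fuller plan, because the test is named and does not fit. The size does rest on assumptions: about 12% per scale if all three pairs are tested unadjusted, and about 8–9% for two contrasts against the initial round, with n of 20–100, correlations of 0.3–0.8, normal data and no true change. If only two rounds are held, the inflation does not arise and the error is in 2.7 and Table 1 instead. Severity: should fix.

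Two further inferences are not supported:
- A reader might multiply across the four scales: 12 independent tests give 1 − 0.95¹² = 46%. That mixes in a separate matter. One correct overall test per scale would still leave four tests, with 1 − 0.95⁴ = 18.5% if independent, and the scales are likely to be correlated.
- A reader might say that dropout biases the pairwise contrasts. Each pair could rest on a different subset of workers, but the article gives no dropout figure, and bias depends on why rounds are missing.

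**What to change.** First, state the same number of rounds in 2.6, 2.7 and Table 1.

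If there are two, keep the paired Wilcoxon test and remove the intermediate evaluation from 2.7 and the follow-up round from Table 1.

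If there are three, correct 2.6 and replace the sentence in 2.7 with one of these:
- One overall test of round per scale at 5%, followed by pairwise Wilcoxon tests only if it rejects. The overall test can be Friedman, or a repeated-measures or mixed model where its assumptions suit the scale; ordinal items such as the EQ 5D-5L dimensions suit a linear model poorly.
- Final minus initial as the single key contrast per scale, tested by paired Wilcoxon and reported with a 95% confidence interval, with the intermediate round descriptive.

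The cost is a sentence or two in the text and no change to data collection if the rounds already match. The price is slightly fewer nominally significant pairwise results. Friedman uses only workers with all three rounds, so it discards more incomplete data than separate pairwise tests; the mixed model avoids this by also using workers with incomplete rounds.

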### 2.8. Ethics and Dissemination

This study protocol was approved by the A Coruña-Ferrol Research Ethics Committee under the number 2019/249, with the date of 24 April 2019. In addition, this protocol was registered in ClinicalTrials under the identifier NCT04584021, on 12 October 2020. It is available at https://clinicaltrials.gov/ct2/show/NCT04584021.

In case any change in the protocol is needed, this will be communicated to the Research Ethics Committee with the assigned reference number. These modifications will be updated in the Clinical Trials register.

The impact that the use of the procedures defined in the project may have on the protection of the personal data of the participants will be evaluated, emphasizing that such data will never leave the information system of the “Tecnología Aplicada a La Investigación en OcupacióN, Igualdad y Salud” (TALIONIS) Group, following the regulations of the Spanish and European Organic Law on the protection of personal data [67,68]. Data confidentiality and anonymity will be maintained through pseudonymization techniques. Once the study is completed, the data will be stored anonymously with the previous authorization of the participants.

The results of the questionnaires and assessment tools will be administered, coded, and managed through the software of REDCap. This platform complies with data protection regulations and stands out for being a widely used tool in clinical trials at an international level. The PI will have access to all the identification data of the participants and all the data collected during the study; the rest of the research team will have access to the data of the participants without identification through the REDCap platform, which allows the capture and consultation of the data anonymously.

The results related to the data of the wearable wristbands will be automatically captured through the wearable wristband data acquisition module. This platform was made following software design standards to guarantee the security and anonymization of the data during capture. It was developed in the Python programming language, along with the necessary libraries for the capture and storage of data in an anonymous way. The data is stored in an SQL server database that, together with the anonymization mechanisms and strategies created by the research team, has data masking mechanisms. In addition, it has limited access to data and security and access control mechanisms. Regarding Bluetooth technology, each bracelet has a unique internal key, generated at random, which is automatically changed. All these software resources are located in a small computer that will be placed in the environment of the center. This computer does not have input and output mechanisms to avoid any person outside the computer trying to access it. The PI will have access to the data related to the identification of the participants, and to the relationship of each participant with the internal number of each wristband. Once the study is finished, this data relationship will be eliminated.

## 3. Discussion

This pilot study may allow us to design a broader study with more participants in future. Stress is increasingly present in our society, and despite being historically understood as an expected effect derived from the mere activity of working, in recent years it has started to be considered as detrimental, but not unavoidable [69,70]. This kind of study could help with the control and detection of stress, influencing positively its reduction and improving the quality of life of workers [37]. In particular, if this study is successful, it would allow the evaluation of occupational stress by using cheap devices and easy-to-understand questionnaires that can be used by any person without any specific training. It would be possible to establish the influence that working stress has on the daily routines and occupational balance of workers.

In addition to the worldwide increase in stress, the emergence of coronavirus disease 2019 (COVID-19) has meant a significant worsening of the mental health of a large part of the population. Stress, along with anxiety and depression, have spread or become more severe during the pandemic in the general population [71]. Job instability due to unforeseeable lockdowns and restrictive measures leads to increased stress in the population, which along with precarious jobs, generates long-term uncertainty that can further increase general stress levels [72,73].

## 4. Conclusions

This project contributes to know the influence of occupational stress on the quality of life in a work environment. Therefore, it is intended to observe some parameters (activity, sleep, and heart rate) recorded through Xiaomi Mi Band 3. In addition, it aims to know about the level of work stress in diverse aspects of daily living, using various online self-report questionnaires in different periods of time. This data obtained from the questionnaires and wristbands will allow to determine the level of stress and its influences on quality of life during and after work.

The increasing use of portable devices such as smartphones or wearable devices encourages to obtain real-time biomedical data available for people, without going to health resources. Thus, this project considers as innovative that all measurements are registered online so that the workers can have an insight into their level of stress, the different stressful factors, and other parameters related to their activity, sleep, and heart rate, which influences their quality of life and work activity. It may help them to be more conscientious about their situation, so they can decide to make changes in their daily routines and habits.

Finally, considering the current pandemic situation, the online registration of all measurements will provide a follow-up of the participants without the need for face-to-face meetings.

## Figures and Tables

**Figure 1 ijerph-18-01413-f001:**
[figure not shown]
Registration and capture of biometric data and the assessment process.

**Table 1 ijerph-18-01413-t001:** Measuring assessment tools.

Instrument	Data	Delivery Phase
EuroQol-5D-5L (EQ 5D-5L)	Quality of life	Beginning, follow-up, and completion
Pittsburgh Sleep Quality Index (PSQI)	Sleep habits	Beginning, follow-up, and completion
State-Trait Anxiety Inventory (STAI)	Anxiety	Beginning, follow-up, and completion
Perceived Stress Scale-10 (PSS-10)	Stress	Beginning, follow-up, and completion
Stress Questionnaire	Work stress factors and daily functioning	Daily (3 items) and weekly (4 items)

## Data Availability

Once the data collection process is finished and these have been coded, structured, and analyzed, these data will be provided, after the Spanish Data Protection Agency’s consent, to any researcher that contacts TALIONIS group Principal Investigator, [name] ([contact]).

## Appendix A

**Table A1 ijerph-18-01413-t0A1:** Weekly and Daily Questionnaire Items.

**Daily Questionnaire**	
**The three following questions, which reflect stress, work commitment, and frustration, will be sent to participants on a daily basis.**	
**Item 1**	How exhausted did you feel today for reasons related to your work?
**Item2**	How motivated were you at work today?
**Item3**	How irritated or frustrated were you today for reasons related to your work?

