Finally, a self-made questionnaire was developed considering the results of a prior poll that assessed different factors potentially related to stress. Those items that were directly related to stress were chosen for the questionnaire. This final questionnaire was agreed on by a stress psychologist professional. It is composed of three daily and four weekly items to answer (Appendix A), related to stress, work commitment and frustration, sleep, physical activity, and occupational balance. All items in the weekly and daily questionnaire are scored from 0 to 5 (0 = Nothing; 1 = Very little; 2 = Little; 3 = Some; 4 = Quite a lot; 5 = A lot).

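### The daily questionnaire as printed gives no way to mark a day not worked, so off-day replies to the work-motivation item cannot be interpreted and could bias day-level associations

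*Protocol article*

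**What the plan says.** **Frequency.** Appendix A introduces the three daily items as questions "which reflect stress, work commitment, and frustration, will be sent to participants on a daily basis". Table 1 repeats the schedule as "Daily (3 items) and weekly (4 items"). Neither place limits the items to working days. Section 2.1 sets follow-up at six months, and section 2.6 has this questionnaire answered throughout the study.

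**Scale.** Section 2.6 states: "All items in the weekly and daily questionnaire are scored from 0 to 5". All six codes are labelled, 0 as nothing and 5 as a lot. None means not applicable.

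**Items.**
- Item 1: "How exhausted did you feel today for reasons related to your work"
- Item 2: "How motivated were you at work today"
- Item 3: "How irritated or frustrated were you today for reasons related to your work"

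**Work schedule.** Working hours and overtime are listed in section 2.6 only on the socio-demographic sheet, which is filled in before other data. No daily record of whether the participant worked is described.

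**Analysis.** Section 2.7 names Pearson or Spearman correlation for pairs of numerical variables and describes a general cleaning step. It states neither the level of analysis (person-day or person mean) nor a rule for non-working days.

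**The concern.** Six months of daily forms necessarily include weekends, public holidays, leave and sick days. On such a day item 2 has no valid answer, and the participant can only enter a number or leave it blank.

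Each choice loses information. A 0 is a legal value, so a general cleaning step has no ground for removing it. A blank looks like a missed form, which matters in a pilot meant to show that its instruments are feasible (sections 2.1 and 2.4), because response rates would be misread.

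There are two further consequences. The objectives relate stress to activity and sleep, and day type may affect both sides of that relation. Section 2.4 also uses the pilot to supply standard deviations for a later sample size, and structural zeros would inflate a day-level standard deviation.

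**Working it through.** The article gives no sample size, effect size or expected score, so there is no figure of its own to reproduce. The check has two parts.

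**1. Which items fail on a day off**

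| Item | Refers to | A 0 on a day off |
|---|---|---|
| 1, exhaustion | feelings attributed to work | can be true |
| 2, motivation | being at work that day | no valid meaning |
| 3, irritation | feelings attributed to work | can be true |

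Only item 2 is clearly invalid. Items 1 and 3 remain answerable, and a non-zero reply is possible too if work strain carries over.

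**2. How large the distortion could be**

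All of these inputs are assumptions:
- Off-days are w = 2/7 of days (weekends only, 52 of 182 days, 29%).
- On working days item 1 has mean 2.5 and SD 1.2, item 2 has mean 3.0 and SD 1.1, and they are independent (true r = 0).
- A share q of off-days is answered with 0 on both items, and the rest are blank.
- Sleep has SD 1 h and is d hours longer on off-days.

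The share of off-day zeros among completed forms is f = wq / (1 − w + wq).

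For pooled person-days:
- cov(1,2) = f(1 − f)·m1·m2
- var(k) = (1 − f)·sk² + f(1 − f)·mk²
- cov(2, sleep) = −f(1 − f)·m2·d, and var(sleep) = 1 + f(1 − f)·d²

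Worked case, q = 1: f = 0.286 and f(1 − f) = 0.204.
- cov(1,2) = 0.204 × 7.5 = 1.53
- var(1) = 0.714 × 1.44 + 0.204 × 6.25 = 2.30
- var(2) = 0.714 × 1.21 + 0.204 × 9 = 2.70
- r = 1.53 / √(2.30 × 2.70) = 0.61

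| q | f | r, items 1 and 2 | Item 1 mean | r, item 2 and sleep (d = 1 h) |
|---|---|---|---|---|
| 0 | 0 | 0 | 2.50 | 0 |
| 0.10 | 0.038 | 0.18 | 2.40 | −0.09 |
| 0.25 | 0.091 | 0.34 | 2.27 | −0.18 |
| 0.50 | 0.167 | 0.48 | 2.08 | −0.26 |
| 1 | 0.286 | 0.61 | 1.79 | −0.34 |

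If sleep does not differ between day types (d = 0), the last column is 0 throughout. At q = 1 it is −0.18 for d = 0.5 h and −0.46 for d = 1.5 h.

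At q = 1 the item 1 SD rises from 1.2 to √2.30 = 1.52 and the item 2 SD from 1.1 to √2.70 = 1.64. The variances are 1.6 and 2.2 times their working-day values.

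*Person-level means* (simulation, 2,000 replicates, 20 or 30 participants, between-person SD 0.7 on both items, true r = 0). With the same off-day share for everyone, mean r is within 0.005 of 0 at every q. With shares spread from 20% to 45%, it is about 0.06 at q = 0.5 and about 0.15 at q = 1.

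With item 2 coded not applicable on off-days, any pair involving item 2 uses working days only. Its spurious correlation is then 0 in every scenario.

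**The case against.** The strongest reply is that the article never says an off-day is coded 0, that an answer is forced, or that off-day forms are completed at all. A reader might infer from the daily schedule and the 0 code that days off enter the data as false zeros. The documents do not support that as fact. Blanks are equally possible, and at q = 0 the correlation bias is nil. This part of the reply stands, so the bias is conditional.

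A reader might also infer that all three items are invalid on days off. The wording of items 1 and 3 does not bear this out, and gating them out would discard genuine answers about carry-over. Lower exhaustion with longer sleep at weekends would be a real day-type pattern that calls for adjustment, not a coding error. This stands as well.

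Weekends can be recognised from form dates and handled in analysis. That is right for workers on a weekday schedule, but it leaves leave, sickness and irregular hours unresolved. A later analysis plan cannot recover what the form did not collect.

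Finally, the article is condensed, the full electronic form may contain branching, and the questionnaire is the last-listed secondary measure in a pilot that also uses PSS-10 and STAI. These points limit the importance. They do not remove the defect, because the items, their frequency and the complete response scale are all printed and leave item 2 without a valid reply.

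**Conclusion.** The point holds in a limited form. As printed, the daily form cannot mark a day not worked, and item 2 has no valid answer on such a day. Zeros and blanks on those days are therefore ambiguous, except where the date alone settles the matter. Items 1 and 3 stay valid but need day type taken into account.

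The size of any bias depends on assumed distributions, on how many off-days are answered 0 and on the level of analysis. For pooled person-days, r for items 1 and 2 runs from 0 with no off-day zeros, through 0.18 at 10%, to 0.61 at 100%. For person-level means it is about 0 to 0.15. It would be wrong to conclude that the plan will produce spurious associations of the larger size, because section 2.7 does not commit to pooled day-level correlation. The ambiguity of item 2 needs none of these assumptions, and it is reason enough to change the form.

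**What to change.** - Add a yes/no question to the daily REDCap form asking whether the participant worked that day.
- If the answer is no, code item 2 as not applicable, distinct from 0 and from missing. Keep items 1 and 3 on all days.
- Analyse item 2 on working days only, and count its response rate against working days.
- Include day type when relating the daily items to wristband sleep and activity.

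The cost is one extra question per day. On days off it takes the place of item 2, so the form is no longer than before. If forms have already been collected, weekend replies can be separated by date, but nothing described in the article would identify leave and sick days afterwards.
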